## Originality and scientific innovation

3

The pilot study by our group (55) showed that a smoking cessation intervention during addiction rehabilitation is associated with a significantly increased perception of self-efficacy and leads to a reduction in the number of cigarettes smoked per day. While much of the literature to date is still derived from animal studies with limited power (16), a new approach to metabolomic studies in humans suffering from SUD is expected to bring advances in the understanding of addiction mechanisms, as well as in diagnostics and treatment. With the proposed steps outlined herein, we are entering new fields in the area of addiction, as well as investigating the microbiome, and contributing to the research in the emerging psychiatric sub-discipline of *Metabolic Psychiatry* (92, 93), which explores the overlap between mental health issues and metabolic dysfunctions. Given the complexity of this research area, this approach could provide valuable insights into the biochemical processes and metabolic changes associated with SUD. Pioneer’s work demonstrates how the metabolomic perspective can lead to a multi-level understanding of psychiatric processes by integrating empirical evidence regarding the relative presence of metabolic molecules in the body, which have relevance and known causal role in central nervous metabolic and signalling processes (as identifiable through metabolic downstream/pathway analyses via bioinformatic databases) with synchronously collected behavioural data from variables such as response to therapy and psychological factors (38, 94).

The empirical investigation of the influential gateway hypothesis (8, 49) also plays a crucial role and by analyzing how the use of one substance influences the transition to other addictive substances, new strategies for prevention and treatment can be developed. Therefore, the extension of the pilot study by the analysis of the metabolomic and gut microbial biomarkers promises to deliver important insights into SUDs, which can be applied to treatment and preventive options.

The expected findings will also provide new foundations for the implementation of smoking cessation in the fields of addiction management and psychiatry and thus contribute to the reduction of therapeutic nihilism and good decision-making in healthcare policy.

### Rationale for selection of this cohort

3.1

The undertaking to study metabolic and gut microbiome factors in SUD patients undergoing smoking cessation is associated with several methodological difficulties. SUD patients constitute a group that is distinct from other populations, characterized by psychiatric comorbidity, history of chronic substance exposure, altered metabolic and inflammatory regulation, and frequent polypharmacy. It must be expected that these factors are the source of significant biological variance, and previous studies that have examined metabolic or gut microbiome factors of cigarette smoking, and cessation, have circumvented this issue by studying non-SUD patients (27, 64, 67). On the other hand, individuals with substance use disorders (SUD) exhibit very high rates of tobacco use, nicotine dependence, and relapse (95), yet the biological mechanisms underlying smoking cessation in this population remain largely unexplored. Moreover, smoking cessation as an add-on therapy holds promise for a surplus value for SUD outcomes and trajectories through a hypothesized reversed *gateway* effect of nicotine cessation.

To date, the research literature lacks interventional RCTs on behavioral smoking cessation interventions including metabolomics and microbiome data in a longitudinal design. If metabolic or metabolomic markers are to inform clinically useful biomarkers or interventions, they must be validated under complex and real-world conditions.

### Innovative aspects of the therapeutic community approach for SUD

3.2

The immanent assumption of the therapeutic community approach (36) is that SUD reflects deeper disturbances in identity and personality structure, values, emotional regulation, and social functioning rather than being only a biomedical dependency. Therefore, the central mechanism of change is “community as method,” meaning that recovery occurs primarily through structured social living, mutual self-help, and social learning processes in which peers provide feedback, role modeling, accountability, and reinforcement of pro-social behavior. The practical approach in a SUD recovery institution – which represents the actual environment for participants of the present study – goes along with structured leisure, work and community activities, as well as meals and exercise. This structure might contribute to social learning and establishing daily routines, a sense of goal-directedness and motivation for sustained drug abstinence (36). But it is also in harmony with metabolic and nutritional psychiatry (93), and microbiome perspectives, as it can be hypothesized that this structured way of life supports the restoration of circadian rhythms, metabolic and gut microbial homeostasis, and normalization of reward circuitry (96, 97).

## Methods and research design

4

### Type and design of the study

4.1

The present study is a randomized controlled experiment in N = 100 SUD- inpatients during a therapeutic community treatment with one intervention group that will receive an additional 6-week smoking cessation intervention and one control group that will receive treatment as usual. The study design consists of a 2 x 2 mixed subject design with repeated measures for the biological analyses and a 2 x 3 mixed subject design with repeated measures for the psychobehavioural analyses (see **Table 1**). In both groups, an examination of metabolic and gut microbial profiles, as well as psychological variables, will take place. Biological parameters will be ascertained from blood and stool specimens for nuclear magnetic resonance (NMR) spectroscopy metabolomic analyses and from stool specimens for 16s-mRNA (hypervariable V3-V4 regions) sequencing and subsequent gut microbial profiling. Psychobehavioural and biological data will be collected pre & post smoking cessation, and additionally, there will be a follow-up measurement of the psychobehavioural variables 3 months upon completion of the study (see **Figure 3**: Consort Flow Chart for further illustration).

**Table 1 T1:** Overview of the statistical design.

Study group	Pre- intervention baseline	Post- intervention after 6 weeks	Follow- up after 3 months
Intervention Group (N = 50)	Psychobehavioural Data	Psychobehavioural Data	Psychobehavioural Data
	Metabolic/Microbial Data	Metabolic/Microbial Data	
Control Group (N = 50)	Psychobehavioural Data	Psychobehavioural Data	Psychobehavioural Data
	Metabolic/Microbial Data	Metabolic/Microbial Data	

green cells: biological data; light brown cells: self-report data.

**Figure 3 f3:**
[figure not shown]
Flow diagram of the trial.

### Recruitment

4.2

The recruitment and examination will involve patients from the association “Grüner Kreis”, who are housed at the Johnsdorf facility. All patients are diagnosed with a form of SUD (F1x.x) by a licensed psychiatrist according to the International Classification of Diseases version 10 (98). Furthermore, participants have to explicitly state that they want to quit smoking. After administering the psychological questionnaires and collecting demographic data, patients will be randomly assigned to either the intervention or control group. The allocation to the groups will be carried out using computer-assisted block randomization (https://www.randomizer.org). The location for the examinations (blood and stool samples) is the Otto Loewi Research Center at the Medical University of Graz. The transfer of participants (Johnsdorf facility – Otto Loewi Research Center/Med Uni Graz) will be carried out by the association’s own buses from Grüner Kreis. Upon completion of data collection, the intervention group will undergo a 6-week smoking cessation program, while the control group will only receive treatment as usual. After the intervention phase, participants will again complete psychological questionnaires, and blood and stool samples will be collected at the Otto Loewi Research Center. Three months later, a follow-up assessment of the psychobehavioural variables will be conducted.

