### Intervention

4.3

During the inpatient stay at the ‘Grüner Kreis’ community, the patients will be allocated to an intervention group and a control group. Patients of the intervention group will take part in an additional 6-week behavioural therapy program for smoking cessation. Patients of the control group will undergo treatment as usual. The standard treatment within this therapeutic community—which all participants will receive—consists of group therapy (once a week), individual psychotherapy (once a week), counseling by social workers, psychiatric consultations, as well as sport-, art- and work therapy. For further information on the principles of therapeutic community-based addiction treatment, see, e.g., DeLeon & Unterrainer (36).

The “smoke free in 6 weeks” program is a standardized behavioural therapy intervention (see Batra & Buchkremer (99) for detailed instructions) that takes place once a week for 1.5 hours over 6 weeks and is provided by the Austrian health insurance provider *Österreichische Gesundheitskasse* (ÖGK). Held in the therapeutic community, it will employ principles of cognitive-behavioural therapy (CBT) coupled with personalized recommendations for nicotine replacement. The Austrian health insurance standard for therapy will be guiding the program’s content, which is tailored for inpatient clients. Specifically, the following interventions based on CBT techniques will be applied in the weekly group sessions consisting of 10 to 15 participants: Psychoeducation including information on tobacco addiction, health risks, advice on relapse prevention and the handling of craving, motivation building, behavioural observation, setting a personal quit-smoking day, behaviour modification through the development of alternative actions, training of progressive muscle relaxation, strengthening of self-efficacy and information on the topics of physical activity and nutrition. Finally, to increase intrinsic motivation, each session will include an analysis using a calibrated carbon monoxide measurement. The primary aim is to help clients achieve smoking cessation, favouring this approach over gradual reduction methods. To support ongoing abstinence and motivation, participants will be directed to additional resources such as the Smoke-Free App, Smoke-Free Phone, and regional outpatient cessation services. This program will be led by a clinical psychologist who is specifically trained in conducting the program.

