#### Dietary assessments

4.4.2

Dietary assessments will be performed using the Vienna Food Record (106) a food frequency questionnaire which takes Austrian-specific eating habits into account. Participants will be asked to document their food intake during the week prior to the assessments of blood and stool.

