### Inclusion and exclusion criteria

4.5

*Inclusion Criteria:* Participants must provide informed consent. They must have a diagnosis of a form of substance use disorder (F1x.x) by a licensed psychiatrist according to ICD-10 (98). Participants must be at least 18 years old, can be of either sex, and must have sufficient knowledge of the German language. All participants must explicitly express their willingness to quit smoking. A minimum duration of abstinence from the primary substance and stable dosage of long-term medications for at least 3 months prior to inclusion is mandatory.

*Exclusion Criteria* include lack of consent, age below 18, or inability to provide informed consent. Participants with acute psychotic symptoms or acute suicidal tendencies are also excluded. Further exclusions are cardiovascular disease, pregnancy or breastfeeding, severe mental or organic illnesses (such as epilepsy, brain tumours, recent major surgery), tumour diseases, dementia (Mini Mental Score <20), severe autoimmune diseases or immunosuppression, acute infections, or acute diarrhea. Individuals with prior gastrointestinal surgery (except appendectomy), probiotic intake within the last 6 months, or those consuming dietary supplements, probiotics, antibiotics, or prebiotic supplements during the study will also be excluded.

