#### Methods of preventing bias

4.7.7

In the present study, several measures are taken to avoid bias. First, randomization is performed to ensure that participants are randomly assigned to the different groups. Furthermore, an experimental design with a control group that receives the usual treatment, allows a comparison with the intervention group. Additionally, all subjects are housed in the same facility where they receive the same treatments, meals, and – for the intervention group – the same smoking cessation intervention. These conditions ensure a high degree of uniformity and standardization, minimizing potential bias. Dietary factors, and confounders such as medication will be considered cautiously and explicitly (see 4.7.2 and 4.7.3).

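### Section 4.2 places only questionnaires and demographics before randomisation, so the baseline blood, stool and food record may be collected after patients know their arm

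*Protocol article*

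**What the plan says.** Section 4.2 (Recruitment) gives one explicit condition for allocation: "After administering the psychological questionnaires and collecting demographic data, patients will be randomly assigned to either the intervention or control group". The text then names the randomisation tool and turns to sampling. The sentence that opens "The location for the examinations (blood and stool samples) is the" gives a site, and the next gives the transport to it. Neither gives a time. The next statement about order concerns the programme: "Upon completion of data collection, the intervention group will undergo a 6-week smoking cessation program".

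Section 4.1 (Type and design of the study) ties the measurements to the programme and not to randomisation: "Psychobehavioural and biological data will be collected pre & post smoking cessation". Table 1 shows one biological measurement before the intervention and one after it, in each arm.

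Section 4.4.2 (Dietary assessments) ties the food record to the sampling: "Participants will be asked to document their food intake during the week prior to the assessments of blood and stool". Section 4.2 does not mention the food record.

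On the setting, section 4.5 requires that "All participants must explicitly express their willingness to quit smoking", and section 4.3 states that "Patients of the control group will undergo treatment as usual". Section 4.7.7 (Methods of preventing bias) begins "First, randomization is performed to ensure that participants are randomly assigned to the different groups" and goes on to the control group, the shared facility and covariates. It does not say when allocation is made or disclosed relative to baseline sampling.

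**The concern.** A baseline is protected by randomisation only if it is measured before allocation, or at least before anyone can act on it. Here the arm is evident once disclosed, because one arm gets a group programme and the other gets nothing extra. All participants have declared that they want to stop smoking.

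Between learning the arm and giving the first sample, patients in the intervention arm may cut down or change how they eat. Controls may smoke more, or try to quit on their own. Sampling needs a 12-hour fast, a venipuncture and a bus journey, so attendance could also differ by arm.

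The biological part of the trial has a single pre-measure, so no earlier sample could reveal such a shift. A patient lost between allocation and sampling has no biological baseline at all. Diet is affected too, because section 4.7.2 treats nutrition as a possible mediator and splits the group effect by it. A food record kept after allocation would carry part of the response to allocation into that analysis.

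**Working it through.** The point concerns the order of steps. The plan gives no figure to reproduce, so the check sets the statements side by side.

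**Order of steps**

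| Step | What the article says about time | Relation to allocation |
|---|---|---|
| Questionnaires, demographics | Done before assignment (4.2) | Before, stated |
| Baseline blood and stool | Site and transport only, described after assignment (4.2); before the programme (4.1, Table 1) | Not stated; after, on the natural reading |
| Food record | The week before sampling (4.4.2) | Not stated; depends on sampling |
| Disclosure of the arm | Nothing | Not stated |
| Programme | After data collection is complete (4.2) | After, stated |

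1. Questionnaires and demographics are already placed before assignment. The data collection that must still finish before the programme is then most naturally the biological sampling.
2. No statement puts blood or stool before assignment. The pre-intervention label in Table 1 fits either order.
3. If sampling follows allocation by less than a week, the food record straddles allocation. If it follows by a week or more, the whole record falls after allocation. Only same-day allocation and sampling would keep the record clear of it.

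**Effect on the contrast**

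Let τ be the true between-arm difference after the programme. Let δ be the between-arm difference (intervention minus control) that allocation itself has caused by the time of the baseline sample. The group x time contrast then estimates

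(post_I − pre_I) − (post_C − pre_C) = τ − δ.

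- If the intervention arm cuts down early, δ has the sign of τ and the contrast shrinks.
- If controls quit on their own before sampling, δ has the opposite sign and the contrast grows.
- If controls smoke more before sampling, δ again has the sign of τ and the contrast shrinks.

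The documents give neither δ, nor the interval from allocation to sampling, nor the time of disclosure. The direction and size of the bias are therefore both open.

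**The case against.** The strongest reply is that the order is inferred. The sampling sentences give a place and not a time, and the pre-intervention label fits sampling before allocation. The flow diagram (Figure 3), which might settle the matter, was not available for this check. A journal article also condenses a fuller protocol. All of this stands, and the inference is weaker still for the food record. It limits the point to what section 4.2 states and omits. But the order of allocation and baseline is a design step that the article itself chose to describe, and its description leaves the biological baseline unprotected.

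A second reply is that the setting dampens the mechanism. Participants are inpatients who share meals, the association's own buses take them to sampling, and a short interval would leave little time for diet or gut flora to shift. This makes a large δ less likely. It does not exclude a change in smoking, which is the exposure under study. The programme runs in groups of 10 to 15, so some wait between allocation and start is plausible, though none is stated.

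A third reply is that the possible reactions pull in opposite directions and that power is ample. The first part is correct and is why no direction is claimed. On power, suppose a share s of the effect is already present at baseline. With λ = f²·N·m/(1 − ρ), f = 0.25(1 − s), N = 100, m = 2 and ρ = 0.5, λ is 25, 16 and 6.25 for s = 0, 20% and 50%, and power is 0.999, 0.977 and 0.697. These shares are assumptions. At modest shares little power is lost, so the harm is mainly bias.

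Two stronger readings are tempting. A reader might infer that loss between allocation and sampling lies outside the planned attrition allowance. Section 4.7.1 gives about 10% with no time window, so the text does not support that. A reader might also put a standardised size on the bias, but any such figure would only restate an assumed share.

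**Conclusion.** The point holds as a weakness in the order of steps, not as a demonstrated bias. Section 4.2 makes randomisation depend only on questionnaires and demographics and describes the biological sampling afterwards. Nothing in the article conceals the arm until the samples are taken.

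Followed in that order, the single biological pre-measure could be shifted, or selectively missing, by arm. The group x time contrasts for metabolites and microbiome, and the dietary analyses, would then be biased in either direction by an amount that cannot be estimated from the documents. The questionnaire outcomes are not affected at baseline.

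The conclusion rests on two assumptions: that the narrative order is the real order, and that patients learn their arm before sampling. It would be wrong to say that the article states outright that samples or food records are taken after allocation. The change is worth making before enrolment or, if enrolment has begun, for the patients still to be randomised.

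**What to change.** Replace the allocation sentence in section 4.2 with wording such as: Patients will be randomly assigned only after the questionnaires, the one-week food record, and the baseline blood and stool samples are complete and logged. If allocation has to be generated earlier for logistical reasons, state that it is disclosed to patients and staff only after that point. Add the same rule to section 4.7.7, and check that Figure 3 shows the same order.

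The visits and the randomisation tool stay as they are. The one small cost is that allocation waits until the sampling visit. If samples are already taken first in practice, the same edit simply corrects the description.

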### Intervention

4.3

During the inpatient stay at the ‘Grüner Kreis’ community, the patients will be allocated to an intervention group and a control group. Patients of the intervention group will take part in an additional 6-week behavioural therapy program for smoking cessation. Patients of the control group will undergo treatment as usual. The standard treatment within this therapeutic community—which all participants will receive—consists of group therapy (once a week), individual psychotherapy (once a week), counseling by social workers, psychiatric consultations, as well as sport-, art- and work therapy. For further information on the principles of therapeutic community-based addiction treatment, see, e.g., DeLeon & Unterrainer (36).

The “smoke free in 6 weeks” program is a standardized behavioural therapy intervention (see Batra & Buchkremer (99) for detailed instructions) that takes place once a week for 1.5 hours over 6 weeks and is provided by the Austrian health insurance provider *Österreichische Gesundheitskasse* (ÖGK). Held in the therapeutic community, it will employ principles of cognitive-behavioural therapy (CBT) coupled with personalized recommendations for nicotine replacement. The Austrian health insurance standard for therapy will be guiding the program’s content, which is tailored for inpatient clients. Specifically, the following interventions based on CBT techniques will be applied in the weekly group sessions consisting of 10 to 15 participants: Psychoeducation including information on tobacco addiction, health risks, advice on relapse prevention and the handling of craving, motivation building, behavioural observation, setting a personal quit-smoking day, behaviour modification through the development of alternative actions, training of progressive muscle relaxation, strengthening of self-efficacy and information on the topics of physical activity and nutrition. Finally, to increase intrinsic motivation, each session will include an analysis using a calibrated carbon monoxide measurement. The primary aim is to help clients achieve smoking cessation, favouring this approach over gradual reduction methods. To support ongoing abstinence and motivation, participants will be directed to additional resources such as the Smoke-Free App, Smoke-Free Phone, and regional outpatient cessation services. This program will be led by a clinical psychologist who is specifically trained in conducting the program.

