A-priori sample size calculations were performed with G-Power (108) (version 3.1.9.6), for a mixed-design ANOVA with one interaction between group (2 groups) and assessments (2 repeated measurements). Considering the effects mentioned above, the mixed-design ANOVA was set rather conservatively for a medium effect size (Cohen’s F = 0.25), a statistical Power (1-β) of 0.9, a α of 0.05, an intra-correlation coefficient of 0.5 and nonsphericity correction of 1, resulting in a minimum sample size of 46 subjects per group, and a critical F = 4.06. Adjusting for expected attrition of about 10%, a total sample size of size of 100 is set. The many (mostly biological) variables measured in this study will expectably require statistical corrections; this will also be compensated by statistical methods exceeding classical linear approaches, namely machine learning feature detection and modelling methods (109).

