#### Statistical analyses of psychological variables

4.7.4

The statistical analyses will be performed in SPSS version 29 (IBM) for general procedures, while specific regression models are handled in R (R core team (121)). For example, t-tests will be carried out for independent and paired comparisons of means between and within groups at different times, respectively, assuming that the continuous data are normally distributed. Chi-square and Fisher’s exact tests, the latter in cases of smaller sample sizes, will be conducted in order to test the associations between categorical variables. The Friedman test shall be used in analyzing non-parametric repeated measures. The main effects of the intervention, time effects, and group x time interaction will be tested using a 2 × 3 two-way repeated measures ANOVA design (group x time), using the Greenhouse-Geisser correction in cases when the sphericity assumption will be violated. The level of significance will be α = 0.05, two-tailed, using Bonferroni adjustment for multiple comparisons. In addition, a repeated measures proportional odds logistic regression model using a generalized estimating equation (GEE) will be applied, assessing the intervention’s effect on CPD treated as an ordinal variable. The GEE model, computed in R using the `repolr` package (122), will contain robust variance estimators that take into account within-subject correlations (**Table 2**).

**Table 2 T2:** Summary of statistical methods and outcomes.

Outcome variable	Domain	Statistical method	Software
Self-efficacy, craving, psychiatric scores	Psychobehavioural	Repeated measures ANOVA, t-tests, Friedman test	SPSS
Cigarettes per day (ordinal)	Psychobehavioural	GEE (Proportional odds model)	R (repolr)
Bacterial diversity indices	Microbiome	Kruskal-Wallis, ANOSIM, db-RDA	R, QIIME
Taxonomic composition	Microbiome	MaAsLin2, ANCOM, LEfSe	QIIME2, R
Metabolite concentrations	Metabolic	PCA, O-PLS-DA, correlation analyses	NMR tools, R
Cross-domain associations	Combined (exploratory)	Correlation and regression	R

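### Only the intervention arm is treated in therapy groups (about 4–5 of them), and neither the described arm comparisons nor the sample size allows for it; type I error exceeds 5% if outcomes correlate within groups

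*Protocol article*

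**What the plan says.** Section 4.2 (Recruitment) describes individual allocation: "patients will be randomly assigned to either the intervention or control group". During the intervention phase, "the control group will only receive treatment as usual". Table 1 in section 4.1 plans 50 people per arm.

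Section 4.3 (Intervention) sets out a weekly programme over six weeks whose techniques "will be applied in the weekly group sessions consisting of 10 to 15 participants". It describes one leader: "This program will be led by a clinical psychologist who is specifically trained in conducting the program".

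Section 4.7.4 tests the psychobehavioural outcomes with t-tests and a 2 × 3 repeated-measures ANOVA. Cigarettes per day are analysed with a GEE model that "will contain robust variance estimators that take into account within-subject correlations". No other level of clustering is mentioned.

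Section 4.7.1 sizes the trial "for a mixed-design ANOVA with one interaction between group (2 groups) and assessments (2 repeated measurements"). There is no design effect. The correlation of 0.5 entered there is the correlation between time points, not a therapy-group ICC.

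The microbiome and metabolome group comparisons in sections 4.7.3, 4.7.5 and 4.7.6 name no therapy-group term. Section 4.7.2 mentions linear mixed models for follow-up adjustment of candidate biomarkers, without giving their random effects. Section 4.7.7 (bias prevention) relies on uniform treatment and does not discuss clustering.

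**The concern.** This is a partially nested design: individual randomisation, with grouping created by treatment in one arm only. People in the same cessation group share sessions, peers and calendar time. Section 3.2 itself presents peer feedback, role modelling and accountability as the way the therapeutic community produces change. Section 4.3 adds shared motivation building and work on self-efficacy, which is also an outcome. Some similarity of outcomes within a group is therefore plausible.

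If it exists, the intervention arm carries less independent information than its head count suggests. A test that treats its members as independent then understates the standard error of the arm difference and rejects a true null hypothesis more often than 5% of the time. Enrolling more patients into groups of the same size does not cure this. What is at stake is a false-positive claim for the intervention.

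**Working it through.** **Inputs from the protocol.** Group size m = 10 to 15 (section 4.3). Intervention arm of 50 (Table 1), so 50/15 = 3.3 to 50/10 = 5, that is 4–5 groups. Analysed size 46 per arm, f = 0.25, correlation 0.5, power 0.90, α = 0.05 and critical F = 4.06 (section 4.7.1).

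**Assumed.** Therapy-group ICC of 0.01 to 0.10, with 0.20 as an extreme for power. The protocol gives none.

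**1. The plan's own sample size.** For the within-between interaction in G*Power, λ = f² × N × 2/(1 − 0.5) = 0.25 × N, with 1 and N − 2 degrees of freedom.
- Total N = 46: λ = 11.5, critical F(1, 44) = 4.06, power 0.912.
- Total N = 92 (46 per group): λ = 23, critical F = 3.95, power 0.997.

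The printed critical F therefore belongs to a total of 46, while the plan reads 46 as a per-group figure. That is a separate point. Here it means that the planned trial has about twice the sample that its own inputs require.

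**2. Standard error.** The design effect in the intervention arm is DE = 1 + (m − 1) × ICC. With equal arms and independent controls, true SE / naive SE = √((DE + 1)/2). The 46 analysed in groups of 12, 12, 11 and 11 give a mean m of 11.5.

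**3. Type I error.** I simulated 200,000 trials per setting with no arm difference, unit variance, those four groups against 46 independent controls, and an ordinary pooled t-test at 5%. At ICC 0 the simulation returned 0.050, as it should.

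| Assumed ICC | DE | SE ratio | True type I error |
|---|---|---|---|
| 0.01 | 1.105 | 1.03 | 0.056 |
| 0.02 | 1.21 | 1.05 | 0.063 |
| 0.05 | 1.525 | 1.12 | 0.081 |
| 0.10 | 2.05 | 1.23 | 0.113 |

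As an upper bound, three full groups of 15 give about 0.09 at ICC 0.05 and about 0.13 at ICC 0.10.

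**4. Power at the plan's effect size.** Under the formula in step 1, f = 0.25 with correlation 0.5 equals a difference in change of 1.0 standard deviation: λ = d² × N/4 = 0.25 × N gives d = 1.0. With 90 analysed (45 per arm) and no clustering, power is 0.997. With m = 12.5 and 2n − 2 degrees of freedom it is 0.993, 0.985 and 0.962 at ICC 0.02, 0.05 and 0.10.

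Satterthwaite degrees of freedom are more severe because they reflect the small number of groups. With 46 per arm and m from 10 to 15, power is then:
- ICC 0.01: 0.98–0.99
- ICC 0.05: 0.91–0.97
- ICC 0.10: 0.79–0.94
- ICC 0.20: 0.59–0.84

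**The case against.** **The ICC may be negligible.** The programme is standardised and one leader is described, which limits therapist variation. At ICC 0.01–0.02 the type I error is only 0.056–0.063. This stands as a limit on the size of the problem. It does not remove it, because a common leader does not remove peer effects and nothing in the protocol supports assuming a zero ICC.

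**Random-effect structure belongs in an analysis plan.** This is true in general, and a separate plan may exist. Here, however, the article names the tests that assume independence and states which correlation the GEE variance covers. The mixed models in section 4.7.2 are a genuine exception: their random effects are unstated, so one cannot say that every analysis ignores therapy group.

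**Controls are not fully independent either.** Both arms live in one community and receive weekly group therapy as standard treatment. That is a further dependence which a model with a group effect in one arm only does not address.

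**The work is described as largely exploratory (section 2).** This lowers the urgency, not the validity of the point.

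**A stronger reading: power is overstated.** A reader might infer this, for example by taking the pilot's d ≈ 0.70 with 45 per arm, where power would fall from 0.91 without clustering to 0.75 at ICC 0.10 (m = 12.5, normal approximation). The documents do not support it against the plan's own target. The sample size is set on f = 0.25, and d ≈ 0.70 appears only as background evidence. At f = 0.25 the planned sample leaves ample margin. Whether f = 0.25 was well chosen is a separate question.

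**Conclusion.** The point holds in a limited form. The grouping of the intervention arm into about 4–5 therapy groups is ignored in the sample size, in the described psychobehavioural tests and in the named microbiome and metabolome group comparisons. If the therapy-group ICC is above zero, arm comparisons made as described are anti-conservative. Over an assumed ICC of 0.01 to 0.10 the true type I error of a nominal 5% test is about 0.056 to 0.113, and up to about 0.13 with the largest groups. The simulation is of a simple two-arm t-test with independent controls; the ANOVA interaction and the biological tests would be affected in the same direction, but their figures were not computed.

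A loss of power below the stated 0.90 at f = 0.25 is not shown unless the ICC is around 0.10 or more, and then only once the small number of groups is reflected in the degrees of freedom. Severity: should be fixed.

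**What to change.** 1. Record a therapy-group identifier for every intervention participant from the first group onward. Reconstructing it later may not be possible.
2. For the main arm comparisons, psychobehavioural and biological, specify a partially nested mixed model: a random therapy-group effect in the intervention arm only, with Kenward-Roger or Satterthwaite degrees of freedom. Make it the main analysis, or at least a pre-specified sensitivity analysis. State the random effects of the mixed models in section 4.7.2.
3. Report the estimated ICC with its uncertainty.
4. Add enrolment wave as a fixed effect only if controls are enrolled in parallel with each therapy group. The protocol does not say whether they are.
5. When the sample size section is next revised, state an assumed ICC and the resulting power.

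The cost is one data field and some analysis-plan wording. The drawback is that with 4–5 groups the variance component will be imprecise, and may be estimated at or near zero, while intervals for the arm effect will widen. An estimate of zero from so few groups should not be read as proof of independence.
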